### Treatment Conditions

All participants will receive their intervention in conjunction with constrained usual care (Freedland et al., 2011). Usual care may involve prescribed components of multidisciplinary interventions (e.g., social work, physiotherapy, occupational therapy, case management, speech therapy, diversional therapy, and/or vocational assistance) except for clinical psychology, as well as regular medical reviews by a rehabilitation physician and/or general practitioner. Participants who persistently report extremely high levels of psychological distress (DASS-21 subscales in the extremely severe range, as measured at the beginning of each session) or express suicidal intent during therapy, will be removed from the study and offered immediate psychological treatment. In addition, the treating clinician will assess participants' ability to attend to the session material whether from cognitive impairment or fatigue and make necessary treatment adjustments with regard to rest breaks and/or rescheduling sessions.

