**Figure 1 F1:**
[figure not shown]
Study flow diagram.

This paper describes the study protocol (Dated September 30, 2019; Protocol Version 1.0) to comply with the Standard Protocol Items: Recommendations for Interventional Trials (SPIRIT) (Chan et al., 2013), see Supplementary Table 1 for Spirit Checklist. The trial will be conducted according to the Consolidated Standards of Reporting Trials (CONSORT) of Electronic and Mobile HEalth Applications and onLine TeleHealth (CONSORT E-HEALTH) statement (Eysenbach, 2011), CONSORT Social and Psychological Interventions (CONSORT-SPI) (Montgomery et al., 2018) guidelines and CONSORT extension for the reporting of non-inferiority trials (Piaggio et al., 2012). The trial has been registered on the Australian New Zealand Clinical Trials Registry (ANZCTRN2619001602112). Refer to Appendix I for more details.

The study will commence immediately following ethics approval and recruitment of participants will continue for ~2 years. The overall duration of the study will be 3 years to allow for those in the wait list control condition to complete the intervention and the follow up assessment, and for data analysis and dissemination of results. To test the efficacy of the intervention, the study will test the following hypotheses:

ACT-Adjust intervention: Participants in the active treatment regardless of delivery (FtF vs. VC) will demonstrate increased psychological flexibility and decreased psychological distress following the intervention, compared to those in the control group (waitlist).eHealth: There will be no differences in primary and secondary outcomes between participants who receive the ACT-Adjust intervention by FtF compared to those who receive it via VC.Sustained treatment effects: Participants in the active treatment condition, ACT-Adjust (VC and FtF), will maintain their gains three months post intervention.

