#### Wait List Control Condition

The wait list control group will receive constrained usual care as discussed above excluding clinical psychology. They will be engaged in their prescribed rehabilitation activities for a period of 13 weeks and then complete the Time 2 assessment (post), at which stage they will be randomized to receive either ACT-Adjust FtF or via VC.

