Each participant enrolled in the trial will receive a Therapy Kit comprising a hardcopy of the ACT-Adjust 2.0 Client Workbook and individually wrapped materials for Session 2 (Chinese finger trap), Session 5 (packet of sultanas), and Session 6 (values card pack). All participants will complete the ACT-Adjust 2.0 program (Table 1), which is comprised of 9 × 1.5 h sessions. The week prior to commencing the program (and before randomization occurs), participants will meet with the treating psychologist in person to complete Baseline assessments. Sessions 1–7 will occur on a weekly basis, and a 2-week break will be placed between Sessions 7 and 8, and a 4-week break between Sessions 8 and 9. If required, sessions may be rescheduled by arrangement between the participant and treating psychologist, and will be rescheduled as soon after the original session as is feasible. Following the completion of Session 9, participants will meet with an independent blinded assessor to complete the Time 2 assessment measures (within 1 week of treatment completions). Three months after completing Session 9, participants will meet again with an independent blinded assessor to complete Time 3 assessment measures.

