			**Study period**								
			**Enrolment**	**Allocation**	**Post-allocation**						
					**Intervention**				**Evaluation**		
Time Points			T1	T1a	T1b	Weeks 1–7	Week 9	Week 13	T2	T3	T4
					VC training	Session 1–7	Session 8	Session 9			
Enrolment		Eligibility screen	X								
		Informed consent	X								
		Randomization		X							
Interventions		ACT-Adjust FtF									
		ACT-Adjust VC			X						
		Wait list Control									
Assessments	Baseline measures	Demographic data	X								
		RBANS	X								
	Primary Outcome measures	DASS-21	X			X^2^	X^2^	X^2^	X	X	X
		AAQ-ABI	X			X^2^	X^2^	X^2^	X	X	X
	Secondary Outcome measures	QOLIBRI	X						X	X	X
		SLP	X						X	X	X
		ELS	X						X	X	X
		SWLS	X						X	X	X
	Other measures	HTRS^1^				X^2, 3^	X^2, 3^	X^2, 3^			
		SRS V.3				X^3^	X^3^	X^3^			
		VCSE-Client				X^3^	X^3^	X^3^			
		VCSE-Therapist				X^3^	X^3^	X^3^			

1 *Items 1-2 administered at end of the session and Item 3 at the beginning of the following of session*;

2 *Measure administered at the beginning of the treatment session*;

3 *Measure administered at the conclusion of the treatment session. AAQ-ABI, acceptance and action questionnaire-acquired brain injury; DASS-21, depression anxiety stress scales −21; ELS, enhanced living scale; HTRS, home task rating scale; QOLIBRI, quality of life after brain injury; RBANS, repeatable battery for the assessment of neuropsychological status; SWSL, satisfaction with life scale; SRS V.3, session rating scale version 3; VCSE, video consulting session evaluation*.

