## Ethics and Dissemination

### Ethical Considerations

Ethical approval for the study was granted by the South Western Sydney Local Health District Human Research Ethics Committee (2019/ETH13152), and local site specific assessments were authorized across trial sites (Liverpool Brain Injury Rehabilitation Unit: 2019/STE16924; Bathurst Health Service: 2019/STE17981; Illawarra Brain Injury Service: 2019/STE17982). Any protocol amendments will be reviewed by the steering committee and then be submitted for approval to the relevant ethics committee, for example, the addition of more recruitment sites. These amendments will also be submitted for approval to the clinical trial registry, ANZCTR.

Confidentiality for participants will be ensured as all measures administered will be deidentified using a unique identifier. The unique identifier will be linked to the participant's name and this personal information stored separately in a password protected spreadsheet located on a secure server at SWSLHD, accessed by only the co-ordinating Chief Investigator (DW) and Research Assistant (SC). Consent forms (paper versions) will be stored separately from measures administered (see below for data storage).

Any incidents of harm will be recorded in a secure file and ongoing management of participants will be undertaken by the psychologist delivering the intervention who will record participants' weekly distress using a self-report measure (DASS-21). In addition, a suicide risk assessment is included in the treatment protocol in the first week of treatment. Some participants will be undertaking other rehabilitation treatment and all participants will have a nominated treating doctor to provide additional support. Participants will be given phone numbers and contact details of support systems between sessions. This will ensure adequate monitoring of participants will occur during the trial. Post-trial care will be maintained by the rehabilitation team at the BIRP or icare treatment team. It is not anticipated any harm will occur from participants receiving this treatment, as both clinical and statistically significant improvements in mood were achieved when the intervention was delivered in previous research (Whiting et al., 2020).

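### The safety rule removes participants from the study, not just from therapy, and before Time 2 it can act only in the two ACT arms

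*Protocol article*

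**What the plan says.** The rule is in the protocol article under Treatment Conditions. It has two triggers: persistent extreme distress ("DASS-21 subscales in the extremely severe range, as measured at the beginning of each session") and suicidal intent voiced in therapy. People who meet the first "or express suicidal intent during therapy, will be removed from the study and offered immediate psychological treatment". The article does not say that only therapy ends, or that later assessments are still sought.

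Other sections show where the triggers can occur:

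- **Table 3, footnote 2** describes the session DASS-21 as: "Measure administered at the beginning of the treatment session".
- **Ethical Considerations** states that "ongoing management of participants will be undertaken by the psychologist delivering the intervention", who also records weekly DASS-21 distress, and that "a suicide risk assessment is included in the treatment protocol in the first week of treatment".
- **Wait List Control Condition** says of that arm: "They will be engaged in their prescribed rehabilitation activities for a period of 13 weeks and then complete the Time 2 assessment (post".

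Hypothesis 1, in the Overview of Study Design and Research Hypotheses, expects participants in active treatment, whatever the delivery mode, to show "increased psychological flexibility and decreased psychological distress following the intervention, compared to those in the control group (waitlist". Data Analysis specifies an intention-to-treat primary analysis. It carries the last recorded measures forward for participants who withdraw or cannot be contacted.

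**The concern.** Stopping trial therapy for a person in crisis and giving immediate care is right. The difficulty is that the same sentence also ends study participation. The person's Time 2 outcome is then given up by rule, even where they would have been willing to be assessed.

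Two features make this more than ordinary dropout. The loss depends on DASS-21, which is a primary outcome. It also falls on one side of the Hypothesis 1 comparison. Eligibility sets a minimum level of DASS-21 distress and no maximum, so people already in the extreme range can enrol. On the wait-list such a person is followed to Time 2, while in either ACT arm the same person can be removed. An intention-to-treat comparison depends on treating the randomised groups alike in follow-up, and this rule does not.

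The point is limited to Time 2 against wait-list. At Time 3 the planned comparison is face-to-face against video, where the rule is the same in both arms. Wait-list participants come under it once they start therapy.

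**Working it through.** **1. Who can be removed before Time 2.** The Randomization section gives 16 face-to-face, 16 video and 24 wait-list participants.

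- Exposed to the rule: 16 + 16 = 32.
- Not exposed: 24, because they have no sessions, no session DASS-21 and no in-therapy suicide risk assessment before Time 2.
- One removal is 1/32 = 3.1% of the pooled ACT arms, or 1/16 = 6.25% of a single arm, against 0/24 on the wait-list.

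**2. Whether Time 2 could still be collected as written.** In the ACT arms, Time 2 is dated from completion of Session 9. A participant removed earlier never reaches Session 9 and so has no Time 2 date. Nothing else in the article restores the assessment.

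**3. What carry-forward would put in its place.** This reads the carry-forward rule as covering removals, which the article does not say outright. Table 3 puts Sessions 1–7 in Weeks 1–7, Session 8 in Week 9 and Session 9 in Week 13. That agrees with the text: "a 2-week break will be placed between Sessions 7 and 8, and a 4-week break between Sessions 8 and 9" (7 + 2 = 9; 9 + 4 = 13). If a session score is carried, its age at Week 13 is:

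| Removal at | Week | Age at Week 13 |
|---|---|---|
| Session 1 | 1 | 13 − 1 = 12 weeks |
| Session 7 | 7 | 13 − 7 = 6 weeks |
| Session 8 | 9 | 13 − 9 = 4 weeks |

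The 12-week figure can apply only to the suicidal-intent trigger, since a single score cannot be persistent. If persistence needs at least two sessions, the oldest score behind a DASS-21 removal dates from Week 2 (13 − 2 = 11 weeks). The four secondary outcomes are not measured between baseline and Time 2, so only their baseline values could be carried, which imputes no change.

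**4. Size.** Let k be the number of removals and g the distance in SD between the carried value and the true Time 2 score. The shift in the pooled ACT mean is k × g / 32. Both k and g are assumptions.

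| k | g = 0.5 | g = 1.0 |
|---|---|---|
| 1 | 0.5/32 = 0.016 SD | 1/32 = 0.031 SD |
| 4 | 2/32 = 0.063 SD | 4/32 = 0.125 SD |

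**5. Direction.**

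- *Last session score carried.* A DASS-triggered removal carries an extremely severe value, so the shift is probably against ACT.
- *Baseline carried.* A simulation assumed SD 1, baseline-to-Time 2 correlation 0.5 and no true effect, and removed the 1 to 5 ACT participants who would have had the worst Time 2 scores. It gave an apparent benefit of ACT of about 0.03 to 0.12 SD. With a true effect of 0.5 SD, the gain at five removals was about 0.04 SD (0.535 − 0.494).

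The sign is therefore not fixed by the plan.

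**6. Scale.** The sample size section uses partial η² = 0.17, so f = √(0.17/0.83) = 0.45. A rough two-group conversion is d ≈ 2f ≈ 0.9. A shift of 0.016 to 0.125 SD is about 2% to 14% of that.

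**The case against.** The strongest reply concerns how much this matters. The rule is a legitimate safety provision and probably acts rarely. No removal rate is given, the direction is undetermined, and the upper figure needs four removals, each a full SD off. Someone whose scores are persistently extreme may still be extreme at Time 2, which would make g smaller than assumed. The exclusion of severe psychiatric illness may also reduce how often the rule acts. All of this stands, and it limits the size claimed.

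A second reply is that wait-list participants in crisis may also leave or receive psychological care, through their medical reviews or treating doctor. Total crisis-related loss then need not be one-sided. That is fair as a matter of practice, but the written removal rule still cannot reach them before Time 2.

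A third is that the full protocol or analysis plan may settle what happens after discontinuation, and which recorded values count as the last ones. That could resolve the carry-forward details. It does not alter the sentence in the article, which states removal from the study.

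Finally, a Time 2 score taken after other psychological treatment mixes ACT with that treatment. This is a real cost of continued follow-up. For an intention-to-treat comparison, an observed score at the planned time is still preferable to an older value put in its place.

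**Conclusion.** The concern holds. As written, the rule discards obtainable Time 2 outcomes in the ACT arms only, partly on the basis of a primary outcome, and so weakens the intention-to-treat comparison in Hypothesis 1. Carry-forward fills the gap without recovering the outcome.

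The exposure, 32 participants against 0 of 24, follows from the text. The 0.016 to 0.125 SD range rests wholly on the assumed number of removals, the assumed gap, and carry-forward applying to removed participants. The effect is small unless removals are frequent, and its direction is open. Nothing is claimed about video against face-to-face. It should be fixed because the asymmetry is built into the protocol and is easily avoided.

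**What to change.** Leave the clinical triggers and the offer of immediate care as they are. Under Treatment Conditions, replace removal from the study with wording such as: *stops trial therapy, remains in the trial, and is approached for the Time 2 and Time 3 assessments unless consent is withdrawn*.

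For these participants, date Time 2 at about 13 weeks after baseline, matching the wait-list, and Time 3 at three months after the planned Session 9. Analyse them as randomised with their observed scores, and report these events by arm.

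The cost is a short amendment and matching consent wording. The blinded Time 2 and Time 3 visits already exist. Some participants will decline assessment, and later scores will partly reflect the other treatment they receive.

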#### Wait List Control Condition

The wait list control group will receive constrained usual care as discussed above excluding clinical psychology. They will be engaged in their prescribed rehabilitation activities for a period of 13 weeks and then complete the Time 2 assessment (post), at which stage they will be randomized to receive either ACT-Adjust FtF or via VC.

#### Intervention: ACT-Adjust 2.0

ACT-Adjust 2.0 is a modified version of the original ACT-Adjust (Whiting et al., 2020), to enable individual delivery (as opposed to group delivery) by FtF and by VC and to overcome identified limitations of the previous treatment protocol (Whiting et al., 2020). These were the length of some sessions, difficulties assessing committed action, the complexity of some metaphors for individuals with a TBI and sustainability of treatment gains. The process of modifying ACT-Adjust, involved consultations with a highly experienced panel of clinical psychologists, with expertise in TBI and ACT and/or VC, who reviewed the original ACT-Adjust treatment protocol and made recommendations for changes. Modifications included reducing the length of some sessions and increasing the number of sessions provided from seven to nine sessions resulting in increased dosage. The original Session 4 was divided into two sessions to separate the observing self/self as context from present moment awareness/mindfulness (now Session 5). Committed action (now Session 7) included the addition of the Goal Attainment Scale (GAS) (Turner-Stokes, 2009) to systematically measure behavioral changes (committed action). The GAS is then reviewed in Sessions 8 and 9 to monitor committed action progress and Session 9 is an additional session to reduce risk of relapse. Additional instructions were also provided in the manual to aid other clinicians in delivering the intervention and a summary of each session's goals was provided at the beginning of each session.

The shortened session times (~60 min) is proposed to assist in reducing fatigue and improving attentional processes for participants with cognitive impairments. The additional relapse prevention session (Session 9), aims to improve sustainability of treatment gains which were not achieved in the original ACT-Adjust clinical trial (Whiting et al., 2020). Metaphors were substituted to be VC compatible and more concrete (e.g., Chinese Finger Trap) enhancing participants' comprehension of the session focus. Further strategies to compensate for participants' cognitive impairments and fatigue after TBI translated from the original ACT-Adjust trial, included reviewing and repeating session material at the beginning of the following session, and provision of a hardcopy of the participant workbook printed in size 14 font, with a Flesch Readability Ease rating of 76.4 and Flesch-Kincaid Grade Level of 4.8. In addition, the therapist facilitates completion of workbook exercises, and session specific text message reminders are provided to facilitate completion of between-session home tasks, and for fatigue management, sessions were scheduled at a time favored by the participant, breaks were provided if required and sessions rescheduled if participants felt unable to attend. A summary of the program content is available in Table 1. The intervention will be delivered throughout New South Wales, Australia, by authors DW, MM, and JW and other trained mental health professionals recruited to the project, using the ACT-Adjust 2.0 Therapist Manual.

**Table 1 T1:** Summary of the ACT-Adjust 2.0 program.

**Session no**.	**Content**
1	**Confronting the Agenda** Introduction to the program—Guidelines and boundaries, reasons to see the psychologist, aims of ACT-Adjust, program outline Administer measures Exercise: Mindfulness activity (Mindfulness of the breath, 2 min) Confronting the agenda—identifying individual issues, workability, breathing, mindfulness exercise Home task—Introduce concept of home tasks, reasons for home tasks and home task contract, home task rating sheet Conclusion—Brief summary of the session
2	**Control is the Problem** Administer measures Exercise: Mindfulness activity (Observing thoughts, 3 min) Session introduction—Review of home task, review of previous session (workability, concept of control) Control is the problem—Normalcy of control, human suffering Exercises: Chocolate cake, Chinese finger trap exercise, Let suffering get close Home tasks—Session 2 home task, home task rating sheet Conclusion—Brief summary of the session
3	**Acceptance and Defusion** Administer measures Exercise: Mindfulness activity (Body scan, 5 min) Session introduction—Review of home task, review of previous session (normalcy of control, human suffering) Cognitive Fusion Exercises: Milk milk milk, Physicalise the thought Home tasks—Session 3 home task, home task rating sheet Conclusion—Brief summary of the session
4	**The Observing Self** Administer measures Exercise: Mindfulness activity (Mindfulness of the breath, 2 min) Session introduction—Review of home task, review of previous session (Defusion—milk milk milk, physicalise the thought) The contextualized self Exercises: Passengers on the bus, Observer Chessboard metaphor Home tasks—Session 4 home task, home task rating sheet Conclusion—Brief summary of the session
5	**Present Moment Awareness** Administer measures Exercise: Mindfulness activity (Observing thoughts, 3 min) Session introduction—Review of home task, review of previous session (self as context, passengers on a bus, chessboard metaphor) Mindfulness education Exercises: Mindfully walking, Eating a sultana Home tasks—Session 5 home task, home task rating sheet Conclusion—Brief summary of the session
6	**Values** Administer measures Exercise: Mindfulness activity (Gratitude, 5 min) Session introduction—Review of home task, review of previous session (mindfulness education, eating a sultana) Values Exercises: Values card sort, Values identification, Significant birthday exercise Home tasks—Session 6 home task, home task rating sheet Conclusion—Brief summary of the session
7	**Values and Committed Action** Administer measures
	Exercise: Mindfulness activity (Body scan, 10 min) Session introduction—Review of home task, review of previous session (values) Setting goals Goal attainment scale (GAS) Home tasks—Session 7 home task, home task rating sheet Conclusion—Brief summary of the session
8	**Review** Administer measures Exercise: Mindfulness activity (Body scan, 8 min) Session introduction—Review of home task, review of course Goal attainment scale (GAS) Exercise: Leaves on a stream Home tasks—Session 8 home task, home task rating sheet Conclusion—Brief summary of the session
9	**Review and Relapse Prevention** Administer measures Exercise: Mindfulness activity (Body scan, 10 min) Review and score GAS Review of program Forward planning and where to next

Where possible, all therapy sessions (both FtF and VC) will be delivered to participants in their homes. Where participants do not have access to a safe, private space in their home, an alternative local site will be arranged by the research team. To facilitate session attendance and home task completion, an automated text messaging service, Appointfix (Freedland et al., 2011), will be used to send appointment reminders to participants the day before each session, and personalized, session-specific home task reminders 2 days after Sessions 1–9, and additional reminders 1 week following Session 7, and 2 weeks following Session 8. See Table 2 for examples of text message templates.

**Table 2 T2:** Automated text message reminders for session attendance and home task completion.

**Message type**	**Content**
Appointment reminder	A reminder about your ACT-Adjust appointment on [Date] at [Start time]. If you are feeling unwell and need to reschedule, please contact <Phone number>.
Home task reminders	[Client's first name], it was great to see you this week for your first session. Don't forget to practice the mindfulness activity and monitor any distressing events over the next week. See you at the next session. [Client's first name], well done on completing Session 2. Don't forget to carry your valued activity card with you this week. See you at the next session.
	[Client's first name], we hope you found this week's session helpful. Remember to practice thinking about your distressing thoughts at least 3 times over the next week. See you at the next session. Well done on completing Session 7, [Client's first name]! Remember to listen to the mindfulness recording at least twice this week and keep working toward your goals from the session.

Each participant enrolled in the trial will receive a Therapy Kit comprising a hardcopy of the ACT-Adjust 2.0 Client Workbook and individually wrapped materials for Session 2 (Chinese finger trap), Session 5 (packet of sultanas), and Session 6 (values card pack). All participants will complete the ACT-Adjust 2.0 program (Table 1), which is comprised of 9 × 1.5 h sessions. The week prior to commencing the program (and before randomization occurs), participants will meet with the treating psychologist in person to complete Baseline assessments. Sessions 1–7 will occur on a weekly basis, and a 2-week break will be placed between Sessions 7 and 8, and a 4-week break between Sessions 8 and 9. If required, sessions may be rescheduled by arrangement between the participant and treating psychologist, and will be rescheduled as soon after the original session as is feasible. Following the completion of Session 9, participants will meet with an independent blinded assessor to complete the Time 2 assessment measures (within 1 week of treatment completions). Three months after completing Session 9, participants will meet again with an independent blinded assessor to complete Time 3 assessment measures.

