### Randomization

The randomization process was performed by a researcher independent of the research team. A computer generated randomization list was generated for each phase of the study using online randomization software, Sealed Envelope (Sealed Envelope Ltd, 2019). The initial randomization had a ratio of 2:3:2 (FtF:WL:VC), with a permuted block size of seven. Following Time 2 Data Collection (13 weeks after Baseline/Time 1), wait list control participants will be randomized to the ACT-Adjust intervention on a ratio of 1:1 (FtF:VC), using a permuted block size of four. The results for both phases were placed in sequentially numbered opaque and sealed envelopes. Following completion of a participant's baseline assessment, the Research Assistant will open the next sequential randomized envelope available to determine the participant's assigned condition. The following allocations are required: ACT-Adjust face-to-face *n* = 16 participants; ACT-Adjust eHealth *n* = 16 participants; Waitlist control *n* = 24 participants.

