### Data Analysis

Data will be entered into SPSS statistics software (IBM Corp, 2019), reviewed for missing data and then screened for normality on all outcome measures and for each treatment group. Prior to the main analysis, between groups comparisons will be undertaken to test for equivalency of the groups using chi-square and *t*-tests. Where participants withdraw or are not contactable for the follow up assessment, the last recorded measures will be carried forward to remaining assessment points for data analysis. Primary analysis will be implemented on an Intention-to-Treat basis, using hierarchical linear mixed models to study the differential effects of each treatment condition. For the post-treatment analyses between the three treatment conditions, analysis will focus on linear time effects, treatment conditions and interactions. Cohen's effect size will be calculated for all analyses. Analyses will focus on the estimated mean differences relative to pre-treatment levels on primary and secondary outcome measures (see Table 3). For the longer-term treatment effects, the non-inferiority of the face-to-face and video consulting will be assessed at the 3-month follow-up.

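### Time 2 and Time 3 in the ACT arms hang on completing Session 9, so no blinded outcome date is fixed for participants who stop therapy early, while wait-list Time 2 is set by the calendar

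*Protocol article*

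**What the plan says.** For the two ACT arms, the section Intervention: ACT-Adjust 2.0 sets Time 2 by an event: "Following the completion of Session 9, participants will meet with an independent blinded assessor to complete the Time 2 assessment measures", and this is to happen "within 1 week of treatment completions". Time 3 is counted from the same event: "Three months after completing Session 9, participants will meet again with an independent blinded assessor to complete Time 3 assessment measures". The section is written as if everyone finishes the nine sessions. Sessions may be moved by arrangement and "will be rescheduled as soon after the original session as is feasible"; no outer limit is stated.

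For the wait list, Time 2 is set by the calendar. Under Wait List Control Condition, participants continue usual rehabilitation "for a period of 13 weeks and then complete the Time 2 assessment (post"). Under Randomization the origin is given: "Following Time 2 Data Collection (13 weeks after Baseline/Time 1), wait list control participants will be randomized to the ACT-Adjust intervention".

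Two other sections expect that some people will not reach Session 9. Treatment Conditions provides for removal from the study during therapy, on DASS-21 scores taken at the start of each session or on expressed suicidal intent. Data Analysis provides for withdrawal and loss of contact by carrying the last recorded measures forward, and also says: "Primary analysis will be implemented on an Intention-to-Treat basis".

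**The concern.** An outcome visit triggered by completing therapy exists, on the wording, only for those who complete it. Someone who leaves therapy after Session 5 but would still see an assessor has no Time 2 or Time 3 date. Every wait-list participant has a Time 2 date.

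What fills the gap matters too. DASS-21 and AAQ-ABI are given before each session by the treating psychologist, who cannot be blinded. Carrying the last recorded score forward could put a mid-therapy, unblinded score in place of a blinded post-treatment one. This can happen only in the ACT arms, since the wait list has nothing but baseline before Time 2.

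Separately, if sessions are rescheduled, Time 2 moves later in the ACT arms and stays at 13 weeks in the wait list. The three-arm analysis rests on linear time effects and their interaction with treatment, so unequal elapsed time could blur that comparison if time is coded by visit.

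**Working it through.** **1. The planned schedule.** Inputs are Table 3 and Intervention: ACT-Adjust 2.0. Baseline is the week before Session 1, so take it as week 0.

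- Sessions 1-7: weeks 1-7
- Session 8: 7 + 2 = week 9
- Session 9: 9 + 4 = week 13
- ACT Time 2: 13 + (0 to 1) = weeks 13-14
- Wait-list Time 2: week 13

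The 13-week wait therefore reproduces the programme length, and the planned gap is 0-1 week.

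**2. Effect of slippage.** The article gives no rescheduling rate. Suppose each of the nine sessions slips by one week with probability p (assumed), pushes later sessions back, and the assessor visit falls evenly within the following week. Mean ACT Time 2 = 13 + 9p + 0.5, and the chance of at least one slip = 1 - (1 - p)^9. The 90th percentile is from simulation.

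| p (assumed) | Mean Time 2, weeks | 90th percentile | At least one slip |
|---|---|---|---|
| 5% | 13.95 | 14.9 | 37% |
| 10% | 14.4 | 15.7 | 61% |
| 20% | 15.3 | 16.9 | 87% |
| 30% | 16.2 | 18.0 | 96% |

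If natural improvement over 13 weeks is 0.2-0.3 SD (assumed), it runs at 0.2/13 = 0.015 to 0.3/13 = 0.023 SD per week. A delay of 1-4 weeks (assumed) then adds 0.015 × 1 = 0.015 to 0.023 × 4 = 0.09 SD to the ACT contrast. That is small beside the effect the trial is planned on (partial η² 0.17, so f = √(0.17/0.83) ≈ 0.45).

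**3. Participants without a fixed date.** Randomization allocates 16 + 16 = 32 to ACT. The article gives no discontinuation rate, so a range is assumed.

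| Stop before Session 9 (assumed) | Of 32 | Per arm of 16 |
|---|---|---|
| 10% | 3.2 | 1.6 |
| 20% | 6.4 | 3.2 |
| 30% | 9.6 | 4.8 |

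**4. What carry-forward would put in their place.** The direction differs by measure and by reason for stopping.

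- QOLIBRI, SLP, ELS and SWLS are taken only at baseline before Time 2. The carried value is no change, which dilutes an ACT benefit.
- DASS-21 and AAQ-ABI also have sessional scores. A participant who improved early and left would carry a favourable score. One removed for persistently extreme DASS-21 scores would carry a very poor one.

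**The case against.** Four points on the other side carry weight.

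- The article condenses Protocol Version 1.0, and the assessment rule may describe only the usual pathway. It does not bar assessing people who stop. Carry-forward is stated for those who withdraw or cannot be reached, which can be read as implying that a reachable participant who stopped therapy is still seen. This stands in part: the claim is that no date is fixed, not that such people will go unassessed. But the rule that is stated gives a site no date to use.
- Timing from the end of treatment is legitimate, because the hypotheses concern outcomes after the intervention. Moving every visit to a fixed date would assess some people before Session 9, the relapse-prevention session. This stands and shapes the fix.
- The arms are planned at nearly the same time, and moved sessions are to be held as soon as feasible. This stands; drift is a possibility of unknown size. Video training has its own slot before Session 1 in Table 3, so extra delay in the video arm in particular is not established.
- DASS-21 and AAQ-ABI are self-reports, which limits what an unblinded administrator can influence. The score would still be given to the participant's own therapist, not to the independent assessor named under Blinding.

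A reader might infer more: that ACT completers would be compared with all wait-list participants, that the bias favours ACT, and that a delivery mode losing more people would look better than it is. The article does not support this. Under its stated intention-to-treat analysis, stoppers stay in with carried values, and on the measures taken only at baseline these work against ACT and against the mode that loses more. Nor is there a Time 3 asymmetry with the wait list. Wait-list participants are re-randomized to therapy after Time 2, and the 3-month comparison is face-to-face against video, both counted from Session 9.

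**Conclusion.** The point holds in a limited form. Time 2 runs on two clocks that agree to within 0-1 week only if no session slips, and the stated rule fixes no Time 2 or Time 3 date for ACT participants who stop before Session 9. Substituting carried-forward values, possibly unblinded sessional ones, weakens the intention-to-treat and blinded-assessment claims. At 3 months the same gap affects the face-to-face versus video comparison if early stopping differs between modes.

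The size cannot be read from the article. Under assumed stopping of 10-30%, about 3-10 of 32 ACT participants are affected, or roughly 2-5 per arm. Under assumed slippage the timing effect is about 0.015-0.09 SD and is secondary. The direction of bias is uncertain. The early-stopper gap is the part that most needs correcting, since outcomes that were never collected cannot be recovered by a later analysis plan.

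**What to change.** - Keep the Session 9 anchor for participants who complete therapy.
- State that every randomized participant is invited to blinded Time 2 and Time 3 assessments regardless of sessions attended. Say whether removal from the study ends therapy within the trial only or outcome assessment as well.
- Assess early stoppers at the dates they would have had on schedule: Time 2 at about 13-14 weeks after baseline, and Time 3 three months after the scheduled Session 9 (week 13 plus about 13 weeks, so about week 26).
- Use one common Time 2 window in all three arms, for example weeks 13-14, and record those who fall outside it because sessions were moved.
- Record actual weeks since baseline at each assessment and use them as time in the mixed model.

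The cost is protocol wording and some effort to retain and schedule people who have left therapy. No visits are added beyond those already planned per participant, and the sample size stays at 56. Estimates may be slightly less favourable if stoppers do worse.
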